#### Adjusted analyses

This analysis will be an unmatched comparison, adjusting for maternal characteristics prior to enrolment for each outcome based on causal diagrams and hypothesised influence on effect estimates.

Sensitivity analyses will determine the strength of unmeasured confounding required to invalidate results.^58 59^ To further assess the robustness of findings to the analysis approach and to evaluate any potential differences in results due to the use of real-world data, we will use our cohort to replicate findings observed in the Building Blocks trial. For each analysis strategy, we will derive trial outcomes for a group of families in the administrative data cohort with the same aggregate baseline characteristics as trial participants.

Stratified analyses and interaction terms will be used to investigate effect modification according to the maternal characteristics in box 1, based on previous evidence suggesting the youngest and most disadvantaged mothers are most likely to benefit from the FNP.

Box 1Maternal characteristics prior to enrolment (Family Nurse Partnership participants) or up to 28 weeks gestation (controls) potentially producing effect modificationMaternal age at enrolment.Ethnicity.Healthcare use prior to enrolment (unplanned admissions and A&E visits, admissions for drug/alcohol abuse, violence or self-harm).^69^Chronic conditions (including mental health conditions captured in hospital data).^70^Educational achievement.Special educational needs.Eligibility for free school meals.Out-of-home care.Area-level deprivation.

To identify contextual factors associated with benefitting from FNP (objective 3), we will explore individual and programme characteristics associated with programme engagement, including maternal characteristics prior to enrolment, nurse characteristics and usual care models in LAs. We will also investigate any differences in FNP effect between LAs and between our cohort and the corresponding Building Blocks trial population (restricted to trial inclusion criteria), to help generalise trial results.

A detailed statistical plan will be written prior to analyses. Statistical models will take into account clustering within LAs, and also among nurses where appropriate. Data will be analysed in Stata. Study results will be reported in accordance with GUILD, STROBE and RECORD guidelines.^60–62^

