**Methods and analysis:**

We will construct a retrospective cohort of all women aged 13–24 years giving birth in English NHS hospitals between 2010 and 2017, linking information on mothers and children from FNP programme data, Hospital Episodes Statistics and the National Pupil Database. To assess the effectiveness of FNP, we will compare outcomes for eligible mothers ever and never enrolled in FNP, and their children, using two analysis strategies to adjust for measured confounding: propensity score matching and analyses adjusting for maternal characteristics up to enrolment/28 weeks gestation. Outcomes of interest include early childhood development, childhood unplanned hospital admissions for injury or maltreatment-related diagnoses and children in care. Subgroup analyses will determine whether the effect of FNP varied according to maternal characteristics (eg, age and education).

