#### Programme delivery: FNP Information System (FNP IS)

The HES cohort will be linked to the FNP IS to obtain information on participation in FNP. The FNP IS is a bespoke system that supports the implementation of the FNP programme in England, provided by NHS Digital under contract to the FNP National Unit on behalf of Public Health England. Data are reported in real time and are used locally by FNP teams and nationally by the FNP National Unit to monitor programme delivery and support quality improvement.

Data collected in the FNP IS include information from the mother and child collected at enrolment (by 28 weeks gestation at the latest, including mother’s age, marital status, living arrangements, education, employment, social care), 36 weeks gestation (including maternal health, alcohol, drugs and smoking), birth (including birth weight and gestational age) and at regular intervals until 24 months after birth (including child health and development, social care and other maternal baseline variables). Information on each visit is also collected (including date, length of visit, family nurse seen and referrals to other services). The FNP IS became functional in 2009, and data quality is reported to be high from 2010 onwards. FNP data have been used in previous research.^48 49^

FNP IS contains maternal and child identifiers at enrolment/birth: name, sex, date of birth, postcode, GP code and NHS number. When mothers graduate from the FNP, pseudonymised data are retained by the FNP National Unit only and identifiers are held solely on secure servers at NHS Digital. Since some identifiers might have changed since enrolment (eg, mother’s name, postcode), identifiers will first be updated using the Personal Demographic Service (PDS) within NHS Digital, so that the most relevant set of identifiers can be used for linkage.^50^

The time span covered by each data source (including look-back, study and follow-up periods) is described in the online supplementary appendix.

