Some healthcare use outcomes—A&E visits and unplanned hospital admissions for any diagnosis—will be reported as descriptive outcomes, since the direction of effect could be interpreted positively or negatively (FNP participation might reduce the need for emergency care or alternatively increase appropriate care-seeking). Nonetheless, they represent important outcomes for understanding the effects of FNP on care-seeking behaviour. Similarly, the potential for surveillance bias to distort the effect of early life interventions on child maltreatment has been discussed extensively:^19 27 53^ indeed, nurse home visiting results in increased contact with nurses, potentially leading to lower thresholds for reporting among participating families than control group families. This bias in ascertainment of maltreatment may dilute or reverse the association between FNP participation and maltreatment. Conversely, it has also been hypothesised that nurse’s closeness to participants may delay reporting of suspected maltreatment.^19^

Maternal outcomes will include unplanned hospital admissions for adversity-related reasons (violence, self-harm and drug/alcohol abuse) after birth and death. As for children, maternal rates of A&E visits and unplanned hospitalisations will be reported as descriptive outcomes. We will also examine the effect of FNP participation on school attendance and achievement after birth, and subsequent pregnancies within 18 months of the first birth ending in live or stillbirths. We will examine subsequent births from a pregnancy within 18 months (rather than 24 months as measured in the Building Blocks trial) because 18-month birth-to-pregnancy intervals are associated with the highest risks of adverse outcomes for women and babies.^54^ However, in addition to the outcomes in table 1, we will validate our findings against the outcomes reported in the Building Blocks trial by examining a range of birth outcomes and subsequent deliveries from pregnancies within 24 months of the index birth.

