#### Propensity score matching

To derive propensity scores, we will construct logistic regression models with FNP participation as the outcome, including as predictors all available maternal characteristics up to 28 weeks gestation (at which point the vast majority of mothers have been enrolled), including looked after status, educational achievement and pre-pregnancy chronic conditions. Matched groups will be formed by matching FNP participants to eligible non-participants with a similar participation propensity score.^55^ Effects will be estimated as the difference in outcomes between matched groups. Multiple imputation will be used to account for missing data where data are expected to be missing at random.^56^

The main analysis will restrict matching within the same LA^57^ and time period in which FNP was offered within that LA. Secondary analyses aiming to achieve more closely matched groups (with potentially smaller numbers) will match, first, within the same LA but in different time periods, comparing outcomes for eligible families before versus after FNP was offered; and second, within the same time period but in different LAs, comparing outcomes for eligible families in LAs that did and did not offer FNP.

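### Maternal covariates have two inconsistent cut-offs: one admits post-enrolment records to the propensity score, the other gives controls a longer window in the adjusted and subgroup analyses

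*Protocol article*

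**What the plan says.** Four places in the protocol article set the end of the covariate window.

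- **Propensity score matching.** The participation model is built "including as predictors all available maternal characteristics up to 28 weeks gestation (at which point the vast majority of mothers have been enrolled"). One limit applies to both groups.
- **Abstract, Methods and analysis.** The second strategy is described as "analyses adjusting for maternal characteristics up to enrolment/28 weeks gestation".
- **Adjusted analyses, opening sentence.** The unmatched comparison works by "adjusting for maternal characteristics prior to enrolment for each outcome based on causal diagrams". A woman who never enrolled has no such date.
- **Adjusted analyses, Box 1.** The candidate effect modifiers are measured "prior to enrolment (Family Nurse Partnership participants) or up to 28 weeks gestation (controls"). One item is "Healthcare use prior to enrolment (unplanned admissions and A&E visits, admissions for drug/alcohol abuse, violence or self-harm").

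The section on the FNP Information System places enrolment "by 28 weeks gestation at the latest", so for most participants it falls earlier. The Introduction has home visits starting early in pregnancy. No section gives controls an index date aligned with enrolment, and Limitations does not raise the matter.

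**The concern.** The two rules conflict, and each has its own fault.

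**Propensity score.** If most participants have enrolled by 28 weeks, a window that runs to 28 weeks covers time under the programme. Care use and diagnoses recorded in that interval may be consequences of FNP. Matching on them could remove part of an effect or introduce bias.

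**Adjusted and effect-modification analyses.** Participants stop contributing at enrolment while controls continue to 28 weeks. Among women with the same recorded history, the control needed more time to reach it and so has, on average, the lower underlying risk. Adjustment then makes FNP look worse than it is. It also blurs the subgroups, because a stratum such as any A&E visit is defined over a different length of time in each arm. Subgroup effectiveness is the study's stated main output.

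**Working it through.** The article gives no figure for this point. Its only calculated figure, 3399 children per group for 9.5% against 7.6% (a 20% relative reduction, 80% power, 5% significance), reproduces exactly with the two-sided pooled formula without continuity correction. This point does not change it.

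**Inputs.** From the article: 28 weeks as the controls' cut-off, maternal hospital history up to 11 years before delivery, A&E data from 2010, births from April 2010 to March 2017, and a 9.5% baseline risk. Assumed, because the article does not give them: enrolment at 12, 16 or 20 weeks, event rates of 0.5 to 1.0 per woman-year, and delivery at 40 weeks.

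**Step 1: unequal windows.** With enrolment at week g, the participant's in-pregnancy window is g/28 of the control's: 43%, 57% and 71%. At equal risk, P(any event) = 1 − exp(−rate × weeks/52). At 0.5 per year this gives 10.9%, 14.3% and 17.5% in participants against 23.6% in controls.

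**Step 2: effect on an adjusted estimate with no true effect.** One million women were simulated, 30% of them participants, with participation unrelated to risk. Frailty U was gamma with shape 1 and mean 1, and outcome risk was 0.095 × (0.5 + 0.5U). A logistic model adjusted for any event in the window.

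| Enrolment week | OR, 0.5/year | OR, 1.0/year |
|---|---|---|
| 12 | 1.07 | 1.10 |
| 16 | 1.05 | 1.05 |
| 20 | 1.03 | 1.04 |
| 28 (equal windows) | 0.99 | 1.00 |

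Standard errors of the log odds ratio are 0.007 to 0.008, and crude odds ratios are 0.99 to 1.01. The artefact disappears when the windows are equal.

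**Step 3: extreme case.** Suppose outcome risk is proportional to a gamma frailty of shape a, events are Poisson at rate r, and groups are balanced on the in-pregnancy count alone. At any given count, the ratio of mean frailty is

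RR = (b + T_control)/(b + T_FNP), with b = a/r.

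At r = 0.8 per year, b is 65 weeks for a = 1 and 130 weeks for a = 2.

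- a = 1: 93/77 = 1.21, 93/81 = 1.15, 93/85 = 1.09.
- a = 2: 158/142 = 1.11, 158/146 = 1.08, 158/150 = 1.05.

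**Step 4: full look-back.** Eleven years is 572 weeks. Controls contribute 572 − 12 = 560 weeks. Participants contribute 544 (enrolment at 12 weeks) to 552 (at 20 weeks), or 97% to 99% of that.

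- a = 1: 625/609 = 1.03 to 625/617 = 1.01.
- a = 2: 690/674 = 1.02 to 690/682 = 1.01.

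**Step 5: A&E visits.** For the last births, about seven years (364 weeks) of A&E data exist. Controls contribute 352 weeks and participants 336 to 344. With a = 1 this gives 417/401 = 1.04 to 417/409 = 1.02. With a = 2 it gives 482/466 = 1.03 to 482/474 = 1.02. For births in the first months of the cohort, A&E history cannot reach back before the pregnancy, so the in-pregnancy figures are the nearer guide.

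**Propensity score.** No size can be given. The article has no data on how FNP changes antenatal care use between enrolment and 28 weeks.

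**The case against.** A reader might infer that FNP mothers and controls are matched on unequal windows. The article does not support that. Box 1 lists effect modifiers for stratified analyses and interaction terms, while matching follows the propensity score section, where both groups share the 28-week limit. The fault in matching is the possible post-enrolment content. The unequal window reaches the adjusted model through the abstract's wording, read together with Box 1.

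A reader might also take the statement that "FNP participation might reduce the need for emergency care or alternatively increase appropriate care-seeking" as an admission that FNP alters antenatal care use. It stands under Outcomes of interest and concerns outcomes after birth. It makes an antenatal effect plausible but does not show one.

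Three further objections carry weight.

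- Most covariates hardly move within a few weeks of pregnancy: ethnicity, prior attainment, special educational needs, free school meals, deprivation and pre-pregnancy chronic conditions. This stands. The problem is confined to time-varying items, mainly care use and newly recorded diagnoses.
- Ratios near 1.2 need balancing on in-pregnancy counts alone, which neither strategy plans. This also stands. A long look-back shrinks the artefact to 1% to 3%, though less so for A&E visits.
- A detailed statistical plan is to follow, and the time span of each data source is in an appendix not shown here. Either may settle the cut-off. But the article has not left the windows open: it states them, and they disagree.

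**Conclusion.** The point holds in limited form. Followed as written, the propensity score can condition on post-enrolment records for most participants, and the adjusted and effect-modification analyses give controls a longer window. The second fault biases modestly against FNP: about 3% to 10% on the odds ratio for an in-pregnancy flag, about 1.2 at the extreme, and about 1% to 3% with a full 11-year look-back. These figures rest on assumed enrolment weeks, event rates and frailty distributions, and on no true effect. The first fault is possible but unquantified. Neither shrinks with sample size, which matters in a study that claims power for small differences and sizes itself on a 20% relative reduction. It should be settled before covariates are derived. The documents do not support the wider reading that every covariate is compromised.

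**What to change.** State one rule in the abstract, Propensity score matching, Adjusted analyses and Box 1. Either of these would serve:

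1. Measure all time-varying covariates and effect modifiers in both groups up to the same pre-exposure gestational point, for example the start of pregnancy (birth date minus gestational age), with the same look-back length.
2. Assign each control an index gestation drawn from, or matched to, participants' enrolment gestation, and close both windows there, again with equal look-back.

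The cost is rewording and re-deriving covariates from data already in the plan, since the 28-week rule already requires the pregnancy to be dated. A start-of-pregnancy cut-off leaves out early-pregnancy information recorded before enrolment. The index-gestation option keeps that information at the price of an assignment step.

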### Limitations

We do not have individual-level data on primary care or the number of visits from health visitors that families receive outside of FNP; however, we will seek local aggregate data on usual care models of health visiting and targeted support for teenage mothers over time to examine how these differed across LAs.

Data on mothers who were offered FNP but declined are not routinely collected. Women who refuse participation may therefore be included in our control group; this may introduce some selection bias, since refusers are likely to differ from FNP accepters in ways that also affect their outcomes. However, propensity score matching sensitivity analyses will restrict controls to women who could not have been offered FNP (either before FNP was offered or in LAs not offering FNP). In the event of remaining unmeasured confounders, grouping refusers with other non-participants may result in an underestimation of FNP effects (if less vulnerable women are more likely to refuse) or overestimation (if more vulnerable women are more likely to refuse). Although individual-level data on refusers are not available, we will obtain data from FNP sites, where available, on the rate and aggregate characteristics of mothers declining participation.

FNP eligibility criteria require enrolment before 28 weeks gestation. Due to a high proportion of missing data on gestational age at first antenatal booking appointment, we will include women who are missing this information as potential controls. Ninety-two per cent of all women present by 20 weeks gestation;^63^ therefore, any resulting bias in results is likely to be small. However, we will also conduct sensitivity analyses restricting the control group to women presenting up to 28 weeks at booking appointment, to match FNP eligibility criteria.

We estimate at least 90% completeness for linkage of HES and NPD. There may be selection bias in the analyses related to education and social care outcomes due to mothers or children who are not linked being different to those whose records are successfully linked.^51^ Nonetheless, data completeness in our cohort is likely to be substantially higher than follow-up rates for medium-term outcomes in most existing trials^15 64 65^ (although the Building Blocks trial in England is also using linkage of routine records for follow-up to the child’s seventh birthday).^31^ Linkage of mother-baby records within HES is high (98%).^38^

## Ethics and dissemination

### Patient and public involvement

In the process of designing our study, we engaged with two groups of mothers (some who had participated in FNP, some who had not). We discussed the use of administrative data for research (including concepts that mothers were not previously familiar with, such as deidentification and data linkage), linkage of health and education data without explicit consent and the use of these data specifically for evaluating the FNP. Workshop participants were supportive of the proposed study and fed back that linking health and education data for mothers and their children was a good idea. Participants strongly agreed with sharing their data so that services could be improved and future mothers could benefit, and wanted to know how their data had been used to benefit others. Mothers were strongly supportive of taking into account maternal education and area, and wider family support for the FNP, in order to understand whether the programme worked. We incorporated these opinions into our study plan by planning to evaluate whether the effect of FNP differs by area and by maternal characteristic.

Our Study Steering Committee includes a teenage mother, who will continue to be consulted throughout the study period. Parent participants will help coproduce information on the study for the FNP and institutional websites and help with interpretation of results and identifying the most appropriate methods of dissemination.

### Dissemination

This study will generate policy-relevant findings on the implementation of the FNP in England and likely benefits to maternal and child health, building on evidence from the Building Blocks trial of FNP. By evaluating outcomes for the 31 000 families enrolled in FNP between 2010 and 2017, our study will determine whether there is evidence of benefits for additional outcomes up to age 7 and within subgroups (including especially vulnerable young mothers and children). Our findings will directly benefit the Health and Social Care sector by providing LAs, commissioners and policy-makers with detailed and up-to-date evidence to inform the ongoing rollout and targeting of early interventions designed to support young mothers and child development.

Our main output will consist of evidence on the effectiveness of FNP for different groups of families. These results will be disseminated to policy-makers and commissioners in collaboration with the FNP National Unit and will inform ongoing research into the adaptation of the FNP in England. We will work with parent representatives to coproduce a range of outputs suitable for families participating in FNP. For academic beneficiaries and other researchers, we aim to publish our main findings in high-quality, peer-reviewed journals as well as present at key conferences. Secondary outputs will include methodological research on the accuracy and reliability of data linkage from health, education and social care sectors, which will inform the use of administrative data by data providers and other researchers.
